In Together 2 we seek to generate an in-depth understanding of different modes of remote group consulting (video and hybrid), surface assumptions (around what these models are meant to achieve) and sociotechnical dynamics (the interplay between technical and social elements) underpinning this relatively novel way of providing care, inform practice and extend theorisation. Informed by our previous work on in-person diabetes group consultations for socioeconomically disadvantaged young people in secondary care (NIHR HSDR-funded, 2016–21)
^
25,
26
^ and in-pandemic research on video group consultations in general practice (Health Foundation-funded, 2020–21)
^
27
^, the following research questions act as our starting point:

1. What is the feasibility and acceptability of video and hybrid group consultations to different population groups? What are their (perceived) implications for access, efficiency and safety in general practice?

2. How do patients, carers and NHS staff experience these new models of care, compared to standard one-to-one service provision and in-person group consultations?

3. What are the costs of introducing video and hybrid group consultations? What is the organisational impact on general practice and other system-level stakeholders?

4. What would be the optimal design of a large-scale evaluation to assess clinical benefits and key outcome/activity parameters?

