### C. Process evaluation (WP3)

The mixed methods process evaluation will use qualitative, quantitative and cost-related measures, based on a comparative case study design in up to 10 clinical sites in England (5 case and 5 comparison sites, primarily from general practice). Case sampling will focus on maximum variation in characteristics such as geographical location, size and digital maturity of the clinical site (digital readiness, capability and infrastructure), patient characteristics (ethnic background, digital literacy/confidence, deprivation) and VHGC delivery format and focus.

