We aim to recruit up to 50 patients per practice who will consent to participate in a survey questionnaire comprising patient experience, satisfaction and healthcare-related outcome components, and to allow research access to their healthcare utilisation data. The survey will be administered online and offline, immediately following VHGC attendance (through a link shared on the same platform, e.g. Microsoft Teams, or in paper format for those attending in person), and will examine both patient experiences which relate directly to VHGCs (e.g. satisfaction with care received, inclusion and access implications, quality and safety of care, need for additional follow-up, travel time saved, time off work avoided etc.) as well as to wider experiences of healthcare in the practice (e.g. satisfaction with 1:1 care, perceptions on access, quality and safety). To develop the survey questionnaire, we will draw on questionnaires piloted in our previous research on patient experiences with video consultations and group clinics. We will also adopt or adapt items from existing surveys such as the GP Patient Survey (
https://gp-patient.co.uk/) and the Primary Care Outcomes Questionnaire (PCOQ)
^
31
^. We also expect new items to be developed. The findings will be used in descriptive analyses to provide a quantitative overview of patient experience of VHGCs.

In addition to the case sites, we will recruit an equal number of comparison practices where VHGCs are not being employed (matched with case sites on location, setting, size, deprivation, QOF). As with case sites, we will aim to recruit 50 patients from each comparison site with recruitment targeted at similar patients as those taking part in VHGCs in terms of age, gender and chronic conditions treated. They will receive a shorter version of the patient survey used in case sites with questions relating only to wider experiences of healthcare at their practice and will be asked to consent to research access to their healthcare utilisation data. Our team will also provide support to any comparison or case sites who choose to administer the Patient Activation Measure (PAM) in the context of local service improvement.

**
*iii. Impact of VHCGs on healthcare utilisation*
**

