We will work with practices to collect data (using Word proformas) on patients’ primary care utilisation including the number, type (staff members involved, e.g. GP, nurse or other healthcare professional, and mode of consultation e.g., in-person, telephone, online) and duration of appointments. We will also obtain secondary care utilisation data from NHS Digital using Hospital Episode Statistics (HES) data. Comparisons will be made between patients at case and comparison sites in terms of number and duration of primary care consultations, number of A&E attendances, outpatient appointments (including numbers or proportion of eligible patients waiting more than six months), hospital admissions, unplanned hospital admissions and hospital admissions for ambulatory care sensitive conditions (conditions for which admissions could, in principle, be avoided by good primary care
^
32
^). Mixed effects models, with random intercepts for practice, will be used to analyse these data with the form of the model appropriate to the outcome (i.e. Poisson models for count of appointments/admissions and linear models for consultation durations). Adjustments will be made for patient factors including age, gender, deprivation, ethnicity and comorbidity status. Given the exploratory nature of this work we have not performed any formal power calculations and will interpret the results accordingly. Rather than focus on the presence or absence of statistically significant differences between groups, the analysis will instead examine confidence intervals as a guide to potential differences between the groups, to guide a larger, definitive study.

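### Poisson mixed models with only a practice intercept leave no room for patient-level overdispersion. The case-comparison interval suffers modestly; patient-covariate intervals and the practice variance suffer more.

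*Protocol article*

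**What the plan says.** All references are to the protocol article. Under Quantitative methods, part iii, the utilisation outcomes are compared between patients at case and comparison sites. The analysis is described thus: "Mixed effects models, with random intercepts for practice, will be used to analyse these data", "with the form of the model appropriate to the outcome". A bracket introduced by i.e. then gives the form: "Poisson models for count of appointments/admissions and linear models for consultation durations". On covariates: "Adjustments will be made for patient factors including age, gender, deprivation, ethnicity and comorbidity status". No patient-level random effect, dispersion parameter, negative binomial model or robust variance is mentioned.

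The design is "up to 10 clinical sites in England (5 case and 5 comparison sites, primarily from general practice"). For case sites, "We aim to recruit up to 50 patients per practice"; for comparison sites, "we will aim to recruit 50 patients from each comparison site".

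The same paragraph calls the work exploratory, reports no power calculation, and says that confidence intervals for group differences will guide a larger study. Research question 4 in the Introduction asks: "What would be the optimal design of a large-scale evaluation to assess clinical benefits and key outcome/activity parameters".

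**The concern.** Conditional on practice and covariates, a Poisson model sets the variance of each patient's count equal to its mean. Utilisation in chronic disease usually has a minority of heavy users, and five adjustment factors are unlikely to explain all of that spread. The model has nowhere to put the excess at patient level, so two things happen:

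- Part of the excess appears as apparent variation between practices.
- Standard errors for anything that varies within practice are too small.

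Three outputs could be affected: the case-comparison interval, which is the stated product of the analysis; the intervals for patient covariates; and the practice variance, a natural input to the design of a later cluster study.

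**Working it through.** The article gives no mean count, dispersion or practice variance, so there is no stated figure to reproduce. The mechanism is checked over assumed ranges.

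**Inputs.** From the article: 5 + 5 practices and m = 50 patients each. Assumed: mean count mu = 6, 1 or 0.2; dispersion a = 0, 0.5, 1 or 2, where Var = mu + a·mu²; true practice variance on the log scale s² = 0, 0.02 or 0.05; no true group difference.

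**1. Practice variance.** The log of a practice mean has variance

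s² + 1/(m·mu) + a/m.

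The Poisson model knows only the middle term, so a/m is credited to practice. With m = 50, a/m = 0.01, 0.02 and 0.04 for a = 0.5, 1 and 2.

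- If s² = 0.02, the inflation is (0.02 + a/50)/0.02 = 1.5, 2 and 3 fold.
- If s² = 0.05, it is 1.2, 1.4 and 1.8 fold.

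Simulation (300 runs per cell, maximum likelihood) at mu = 6 and s² = 0.02 gives a mean Poisson estimate of 0.015 at a = 0, and 0.024, 0.031 and 0.049 at a = 0.5, 1 and 2. The rises of 0.009, 0.016 and 0.034 are close to a/50. At a = 1 the negative binomial model gives 0.013. That removes the inflation but lies below 0.02, as does the Poisson estimate with no overdispersion (0.015): maximum likelihood with ten practices is biased down.

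**2. Case-comparison interval.** Exposure is at practice level, so the variance of the log rate ratio is (2/5)·[s² + 1/(m·mu) + a/m]. At mu = 6, a = 1, s² = 0.02:

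0.4 × (0.02 + 0.0033 + 0.02) = 0.0173, so the SE is 0.132.

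The mean fitted SE is 0.114 (Poisson) and 0.118 (negative binomial), with coverage of 88% and 91% for the nominal 95% z interval. Both SEs fall short of 0.132, so most of the deficit is not due to the Poisson form.

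- Over the whole grid, Poisson coverage is 86-96% with overdispersion and 91-96% without it. With t on 8 degrees of freedom it is 91-99%.
- In the individual cells at mu = 1 and 0.2, negative binomial coverage runs from 1 point lower (93.0% to 92.0% at mu = 1, a = 0.5, s² = 0.02) to about 5 points higher (90.7% to 96.0% at mu = 1, a = 2, s² = 0).
- A separate simulation (150 runs per cell, means 0.4-6, dispersion 1-2.5, s² = 0.02) gives 84-91% for Poisson and 87-97% for negative binomial, a gain of about 3 to 7 points.
- Monte Carlo error near 90% coverage is √(0.9 × 0.1/300) = 1.7 points in the first set and √(0.9 × 0.1/150) = 2.4 points in the second.
- With no practice intercept at all, coverage falls as low as 29%, which shows how much the planned intercept protects.

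**3. Patient covariates.** For a covariate that varies within practice, the Poisson SE is too small by √(1 + a·mu), so expected coverage is 2Φ(1.96/√(1 + a·mu)) − 1. The simulated column comes from 500 runs per cell with fixed practice intercepts.

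| mu | SE too small by (a = 0.5 to 2) | Expected coverage | Simulated coverage |
|---|---|---|---|
| 6 | √4 = 2.00 to √13 = 3.61 | 67% to 41% | 67% to 39% |
| 1 | √1.5 = 1.22 to √3 = 1.73 | 89% to 74% | 89% to 73% |
| 0.2 | √1.1 = 1.05 to √1.4 = 1.18 | 94% to 90% | 94% to 91% |

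**4. Reuse for design.** Suppose the inflated variance were put into a Poisson-only formula for a study with M patients per practice. The ratio of assumed to true variance of a practice mean is

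[s² + a/50 + 1/(mu·M)] / [s² + (1/mu + a)/M].

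At mu = 6, a = 1, s² = 0.02:

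- M = 20: 0.0483/0.0783 = 0.62
- M = 50: 0.0433/0.0433 = 1.00
- M = 200: 0.0408/0.0258 = 1.58

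Over mu = 6 and 1, a = 0.5 to 2 and s² = 0.02 and 0.05, the range is 0.53-0.88 at M = 20 and 1.13-1.97 at M = 200.

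**The case against.** A reader might infer that the figures handed to the definitive study will be wrong. The article does not support that. The only product of this analysis that it says will guide the larger study is the confidence interval for the group difference, and the practice intercept largely protects that interval. No practice variance, intracluster correlation or dispersion parameter is promised, and research question 4 names none. The other stated design input is the value of information analysis in the Health economics evaluation section. This objection stands: the harm in step 4 is conditional on reuse.

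The covariates enter only as adjustments, and the article does not say that their effects will be reported. That also stands, so the harm in step 3 arises only if someone reads those intervals.

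The alternative is imperfect too. In the cell shown, the negative binomial practice variance averages 0.013 against a true 0.02, which is 35% low. Some negative binomial fits at mu = 6, a = 2 did not converge properly and are not used here. With 8 degrees of freedom, a chi-square 95% interval for a practice variance runs from about 0.46 to 3.7 times the estimate, so a twofold bias lies within its imprecision. This limits what the remedy can deliver, but it does not favour a model with no dispersion term.

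Finally, the article promises a form suited to the outcome. Its bracket is not exhaustive, since a proportion waiting over six months is also listed, and a fuller analysis plan may handle dispersion. That softens the point without removing it: for counts, the published text does name a form, and that form is Poisson.

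**Conclusion.** The point holds as a minor one. The named model has no term for overdispersion that is very likely, though no figure in the article demonstrates it and the planned adjustment may remove part of it.

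- **Case-comparison interval:** modestly too narrow, by a few points of coverage (about 3 to 7 in one set of assumed scenarios, and from no gain to about 5 in the wider grid). Part of the undercoverage comes from having ten practices and remains under either model.
- **Patient-covariate intervals:** clearly too narrow at means of 1 to 6, little affected at 0.2.
- **Practice variance:** inflated by about dispersion/50. How large that is in relative terms depends on the unknown true value.

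The inflated variance is about right for a design with 50 patients per practice and misleading at other sizes. Nothing in the article shows that it will be used in that way.

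**What to change.** In Quantitative methods, part iii, replace the reference to Poisson models for counts with negative binomial mixed models, or Poisson with an added patient-level random effect. Keep the practice random intercept. State in advance what will be used if a rare outcome does not converge, for example a quasi-Poisson or robust-variance analysis. If the practice variance is reported for design purposes, give it together with the dispersion parameter, both with intervals, and say that ten practices estimate it imprecisely.

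The cost is one changed phrase, one extra parameter per outcome and occasional non-convergence. No new data are needed.

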**Methods:**

Mixed-methods, multi-site research study using co-design and participatory methods, from qualitative, quantitative and cost-related perspectives. WP1 includes a national, cross-sectional survey on VHGC provision across the UK. In WP2 we will engage patients and general practice staff in co-design workshops to develop VHGC models with emphasis on digital inclusion and equity. In WP3 we will carry out a mixed-methods process evaluation in up to 10 GP practices across England (5 sites already running VHGCs and 5 comparison sites). Qualitative methods will include interviews, focus groups and ethnographic observation to examine the experiences of patients, carers, clinical and non-clinical NHS staff, commissioners and policy-makers. Quantitative methods will examine the impact of VHGCs on healthcare utilisation in primary and secondary care, patient satisfaction, engagement and activation. We will also assess value for money of group and individual care models from a health economics perspective.

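### The non-randomised utilisation comparison names no baseline utilisation and no before/after contrast, so pre-existing differences in care use can appear as a VHGC effect

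*Protocol article*

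**What the plan says.** In the protocol article, Quantitative methods, subsection iii (healthcare utilisation) defines the contrast: "Comparisons will be made between patients at case and comparison sites in terms of number and duration of primary care consultations". Several secondary care outcomes follow, covering emergency attendances, outpatient appointments and types of admission.

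For the model it states: "Mixed effects models, with random intercepts for practice, will be used to analyse these data with the form of the model appropriate to the outcome". Counts get Poisson models and durations get linear models. For covariates it states: "Adjustments will be made for patient factors including age, gender, deprivation, ethnicity and comorbidity status".

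Primary care data come from proformas completed with the practices. For hospital data: "We will also obtain secondary care utilisation data from NHS Digital using Hospital Episode Statistics (HES) data". No observation window is given for either source.

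The groups are described elsewhere:
- The Abstract (Methods) plans "5 sites already running VHGCs and 5 comparison sites".
- Subsection ii surveys case patients "immediately following VHGC attendance" and asks the same patients for access to their utilisation data.
- Comparison practices are to be "matched with case sites on location, setting, size, deprivation, QOF", with "recruitment targeted at similar patients as those taking part in VHGCs in terms of age, gender and chronic conditions treated".

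Subsection iii calls the work exploratory, gives no power calculation, and will read confidence intervals rather than significance tests, with a view to a later definitive study.

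**The concern.** Nobody is allocated to VHGCs. The practices had already chosen to run them. The case patients chose to attend, and subsection i will itself count invited patients who did not. No equivalent qualifying event is stated for comparison patients.

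Practices can differ in how readily they offer appointments, and patients in how readily they seek them. Age, gender, ethnicity, deprivation and comorbidity measure neither directly. A patient's own earlier use of the same services is the most direct available measure of both, and the plan does not mention it.

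The estimates are meant to inform the next study. A confidence interval expresses sampling error only. If it is centred on a difference that existed before any VHGC took place, it misleads that study, and reading intervals instead of p-values does not help.

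**Working it through.** **1. Is baseline use handled anywhere?** The places where it could appear are:

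| Place | Content | Prior utilisation? |
|---|---|---|
| Covariates (subsection iii) | five named patient factors | not named |
| Model terms (subsection iii) | random intercept for practice | no period or group-by-period term |
| Practice matching (subsection ii) | five practice characteristics | not named |
| Patient targeting (subsection ii) | age, gender, chronic conditions | not named |
| Data collection (subsection iii) | proformas and HES | no look-back stated |

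**2. Does the random intercept remove the problem?** Write the model as log E(Y) = a + b·G + covariates + u, where G is the group and u the practice effect. G is constant within a practice, so b is estimated from between-practice differences, and u is assumed unrelated to G. If the groups already differ by a ratio r given the covariates, the estimate targets b + ln r. The random intercept widens the interval but does not re-centre it.

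**3. How large could it be?** The plan states no figure for this comparison, so there is none to reproduce. What follows is illustration only.

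Inputs from the document: 5 v 5 practices and 50 patients each, so 5 × 50 = 250 per group and 500 in total (the plan's maxima).

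Assumed inputs, not in the document:
- no true VHGC effect
- mean of 6 consultations per period
- gamma frailty of shape 2, shared by the earlier and later periods
- between-practice SD 0.1 on the log scale
- one adjusted covariate
- 400 runs per setting
- a Poisson model with practice-clustered intervals standing in for the random-intercept model

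| Pre-existing ratio r | Planned adjustment: mean RR | Coverage of 1.0 by the 95% interval | Adding log prior count: mean RR | Difference-in-differences: mean RR |
|---|---|---|---|---|
| 0.80 | 0.80 | 36% | 0.94 | 1.00 |
| 1.00 | 0.99 | 90% | 1.00 | 1.00 |
| 1.10 | 1.10 | 78% | 1.03 | 1.00 |
| 1.25 | 1.25 | 32% | 1.06 | 1.00 |
| 1.50 | 1.50 | 2% | 1.10 | 1.00 |

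Coverage at r = 1.00 is already 90% rather than 95%, so that row is the benchmark for the others.

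At r = 1.25, adding the prior count leaves ln(1.057)/ln(1.25) = 0.055/0.223, about 25% of the bias on the log scale. A single period's count measures a patient's underlying rate with noise. Difference-in-differences returns (ln θ + ln r) − ln r = ln θ, where θ is the true rate ratio. It succeeds here because r was made stable over time.

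**4. Bias against the standard error.** Use SE(ln RR) = √[(2/5)(τ² + (1/μ + 1/k)/50)], with assumed mean μ = 8, dispersion k = 1.5 and between-practice SD τ = 0.10 to 0.20.

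- Patient-level term: (0.125 + 0.667)/50 = 0.0158.
- τ = 0.10: √(0.4 × 0.0258) = 0.102.
- τ = 0.20: √(0.4 × 0.0558) = 0.149.

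A pre-existing 15% difference is ln(1.15) = 0.140, which is 0.140/0.102 = 1.4 SE or 0.140/0.149 = 0.94 SE.

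**5. Precision gain from baseline adjustment.** With an assumed period-to-period correlation of 0.5 to 0.7, the linear-model rule r² removes 25% to 49% of the patient-level term only; the τ² term stays.

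- τ = 0.10: the SE falls from 0.102 to 0.094 or 0.085, about 8% to 16%.
- τ = 0.20: the SE falls from 0.149 to 0.144 or 0.139, about 4% to 7%.

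**The case against.** The strongest reply is that this is a condensed article. The covariate list is introduced in a way that leaves it open, a fuller plan may exist, and look-back windows are commonly left to such a plan. That stands in part. The document does not exclude baseline use, and a reader who infers a closed list goes too far. But the article does state the contrast, the model and the main covariates, and nothing in it points to a baseline period.

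A reader might also infer that outcomes are collected only after the VHGC. The text does not say so; it gives no window in either direction. Nor does it support saying that earlier differences will be read as an effect. Matching, targeting and adjustment may remove much of them, and what remains is unknown.

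The exploratory label is a fair limit on severity. The stated caution, however, concerns power and significance testing, not confounding, and the subsection heading speaks of impact.

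Two further claims are tempting and should not be made. One is a large gain in precision: 25% to 49% describes patient-level variance only, and the SE gain is about 4% to 16% under the assumed inputs. The other is that the index condition must be added as a fixed effect. Comparison patients are already targeted on the chronic conditions treated, and with about ten practices such terms could use up scarce between-practice degrees of freedom.

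Finally, the burden is real. A second period of proformas for up to 500 patients is work for practices, and some baselines may fall in the pandemic.

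**Conclusion.** The point holds as a recommended improvement, not as a demonstrated bias. In a non-randomised comparison of attenders at adopter practices with patients elsewhere, the plan names no baseline utilisation and no before/after contrast. Differences in care use that escape the covariates, matching and targeting can pass almost unchanged into the estimate, and the intervals would not show it.

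Under the assumed inputs, a residual 15% difference would be roughly 0.9 to 1.4 standard errors. The simulated figures rest on the same kind of assumption and on a pre-existing difference that is stable over time. The actual size and direction cannot be derived from the document. The case for change rests on bias rather than on precision.

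**What to change.** 1. For the same consenting patients, extract the same HES and primary care outcomes for a defined period, for example 12 months, before each case patient's first VHGC. Because the case sites already run VHGCs, recruitment is not a suitable baseline date.
2. Give each comparison patient a matched index date so that both groups have comparable periods before and after.
3. Report a group-by-period (difference-in-differences) contrast alongside a model adjusted for baseline utilisation. The adjusted model alone leaves part of the bias; the contrast relies on the pre-existing difference being stable.
4. State how many baselines fall in the pandemic period, when use may have been atypical.
5. Describe the results as associations, and extend the stated caution from power to confounding.

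The cost is longer proformas for practices and a wider window in the consent wording and data request. No extra patients are needed. If the proforma burden is limiting, do this at least for the HES outcomes.
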